6.3 Trial Participants

## 6.3.1 Overall Description of Trial Participants

Healthy 6-12 week old male and female infants born between 37 and 42 weeks of gestation would be recruited in four centres in the United Kingdom (Oxford, London, Bristol and Southampton) and one centre in Malta.

## 6.3.2 Inclusion Criteria

- Healthy male or female infants aged 6-12 weeks at the time of the first vaccination and who were born between 37 and 42 weeks of gestation
- Infants who are known to be free from medical problems as determined by a medical history and clinical examination
- Parents or guardians who are willing for their child to participate and who would be expected to comply with the requirements of the protocol
- Parents/guardians who have given informed consent for their child’s participation in the study

6.3.3 Exclusion Criteria

The participant may not enter the study if ANY of the following apply:

- History of invasive meningococcal C disease
- Previous vaccination against meningococcal serogroup C disease
- Planned administration/administration of vaccines, since birth, other than the study vaccines (with the exception of oral rotavirus vaccine, Hepatitis B vaccine, Hepatitis A vaccine, Influenza vaccines and BCG, that can be administered 14 days before or after study vaccines and Varicella vaccine that can be administered 14 days before or after study vaccines or 4 weeks before or after other live vaccines, i.e. MMR. Varicella vaccine can also be given in the form of the combined Measles Mumps Rubella Varicella vaccine from 13 months of age).
- Receipt of investigational vaccines/drugs, other than the vaccines used in the study, within 30 days prior to receiving the first dose of the vaccines or their planned use during the study period, until 1 month after the administration of the final study vaccine (ie at 12 months of age).
- Confirmed or suspected immunosuppressive or immunodeficient conditions, including human immunodeficiency virus (HIV) infection.
- A family history of congenital or hereditary immunodeficiency.
- Receipt of more than 2 weeks of immunosuppressants or immune modifying drugs, (e.g. prednisolone >0.5mg/kg/day)
- History of allergy to any component of the vaccines.
- Major congenital defects or serious chronic illness.
- History of any neurologic disorders or seizures
- Acute disease at the time of recruitment as defined by the presence of a moderate or severe illness with or without fever (with the exception of minor illnesses such as diarrhoea, mild upper respiratory infection without fever). In such situations enrolment should be postponed until the participant has recovered.
- Administration of immunoglobulins and/or any blood products since birth or planned administration during the study period
- Parents who plan to move out of the geographical area where the study would be conducted.

## 6.3.4 Elimination criteria during the study

The following criteria will be checked at each visit subsequent to the first visit and if any become applicable during the study, it will not require withdrawal of the participant from the study but may determine the participant’s evaluability in the completer’s population (CP) analysis, in which case the data would be included in the Intention to Treat (ITT) analysis.

- Use of any investigational or non-registered product (drug or vaccine) other than the study vaccine(s) during the study period, until 1 month after the administration of the final study vaccine (ie at 12 months of age).
- Chronic administration (defined as more than 14 days) of immunosuppressants or other immune-modifying drugs during the study period. (For corticosteroids, this will mean prednisone, or equivalent,  0.5 mg/kg/day. Inhaled and topical steroids are allowed.)
- Administration of a vaccine not foreseen by the study protocol during the period starting from 30 days before each dose of vaccine(s) and ending 30 days after.
- Administration of immunoglobulins and/or any blood products during the study period.
- Administration of any of the vaccines used in the study outside of the stipulated time period
- Administration of any of the vaccines used in the study in an incorrect limb

### 6.3.5 Delaying criteria during the study visits

Participants with an acute illness would be recruited after the illness has resolved.

Vaccine administration will be delayed in case of acute illness or axillary temperature >38oC.

Venesampling will be delayed for 1 week after the stopping of antibiotics in order to avoid interference with the MenC rSBA assays.

### 6.3.6 Study Procedures

The schedule of the following procedures has been listed in Appendix B.

**Detailed description of study visits**

**i) Visit 1: Study Day 0: First vaccination visit (6-12 weeks)**

- Written informed consent is obtained from the participant’s parent/guardian.
- Inclusion/exclusion criteria will be checked prior to enrolment.
- A medical and vaccination history will be taken and recorded
- Any concomitant medications which are not listed in the exclusion criteria and thus allowed by the study protocol will be recorded.
- Pre-vaccination assessment of body temperature
- Randomisation
- Vaccination: intramuscular administration of one dose of the vaccines used in the study (according to group) will be administered as described in section 7.
- Explanation of diary cards to assess local and systemic adverse events for 4 days following vaccination

The vaccinees will be observed closely for at least 15 minutes, with appropriate medical treatment readily available in case of a rare anaphylactic reaction following the administration of vaccines.

The subjects’ parents/guardians will be instructed to contact the investigator immediately should they manifest any signs or symptoms they perceive as serious.

**ii) Visit 2: Study Month 1: Vaccination visit, at approximately 3 months of age (28-42 days after visit 1)**

- Reporting of SAEs that might have occurred since the last visit.
- Collection of diary card
- Check of elimination criteria.
- Check of contraindications.
- Recording of any concomitant immunosuppressive medication or vaccines not foreseen by the study protocol
- Pre-vaccination assessment of axillary body temperature.
- Vaccination: intramuscular administration of one dose of the vaccines used in the study (according to group) will be administered.
- Explanation of diary card to assess local and systemic adverse events for 4 days following vaccination

The vaccinees will be observed closely for at least 15 minutes, with appropriate medical treatment readily available in case of a rare anaphylactic reaction following the administration of vaccines.

The subjects’ parents/guardians will be instructed to contact the investigator immediately should they manifest any signs or symptoms they perceive as serious.

**iii) Visit 3: Study Month 2: Vaccination visit, at approximately 4 months of age (28-42 days after Visit 2)**

- Reporting of SAEs that might have occurred since the last visit.
- Collection of diary card
- Check of elimination criteria.
- Check of contraindications.
- Recording of any concomitant immunosuppressive medication or vaccines not foreseen by the study protocol
- Pre-vaccination assessment of axillary body temperature
- Vaccination: intramuscular administration of one dose of the vaccines used in the study (according to group) will be administered.
- Explanation of diary card to assess local and systemic adverse events for 4 days following vaccination

The vaccinees will be observed closely for at least 15 minutes, with appropriate medical treatment readily available in case of a rare anaphylactic reaction following the administration of vaccines.

The subjects’ parents/guardians will be instructed to contact the investigator immediately should they manifest any signs or symptoms they perceive as serious.

**iv) Visit 4: Study Month 3: Blood sampling visit, at approximately 5 months of age (28-42 days after visit 3)**

- Reporting of SAEs that might have occurred since the last visit.
- Collection of diary card
- Check of elimination criteria.
- Recording of any concomitant immunosuppressive medication or vaccines not foreseen by the study protocol
- Collection of blood for serology (and B cells studies on a subset of participants): 5.0 ml of whole blood. If less than 4mL of blood is collected, the whole sample will be used serology assays. If 4-5mL of blood is collected the sample will be split in half and shared evenly between serology assays and B cell studies. 2-2.5mL whole blood will provide about 1mL of serum for serology.

The subjects’ parents/guardians will be instructed to contact the investigator immediately should they manifest any signs or symptoms they perceive as serious.

**v) Visit 5: Study Month 10: Vaccination visit, at 12 months of age (51 – 58 weeks)**

- Check of exclusion criteria.
- Check of elimination criteria.
- Check of contraindications.
- Assessment and recording of medical history and vaccination history.
- Recording of any concomitant medication or vaccines not foreseen by the study protocol
- Retrospectively reporting of SAEs that might have occurred since the last visit of the primary phase.
- Pre-vaccination assessment of body temperature
- Collection of blood for serology (and B cell studies on a subset of participants): 7.5 ml of whole blood. If less than 4mL of blood is collected, the whole sample will be used serology assays. If 4-6mL of blood is collected the sample will be split in half and shared evenly between serology assays and B cell studies. If >6mL of blood is collected, 3mL will be used to provide at least 1mL of serum for serology assays, and the remainder will be used for B cell studies.
- Vaccination: intramuscular administration of one dose of the Hib-MenC vaccine and one dose of PCV13
- Explanation of diary card to assess local and systemic adverse events for 4 days following vaccination

The vaccinees will be observed closely for at least 15 minutes, with appropriate medical treatment readily available in case of a rare anaphylactic reaction following the administration of vaccines.

The subjects’ parents/guardians will be instructed to contact the investigator immediately should they manifest any signs or symptoms they perceive as serious.

**vi)** **Visit 6: Study month 10: Blood sampling visit, at 6 days following Hib-MenC booster vaccination (Performed on 256 participants; all participants in the control group and 64 participants each from the Two Dose MenC, Single Dose MenC-CRM197 and Single Dose MenC-TT Groups as determined by randomisation at enrolment).**

- Reporting of SAEs that might have occurred since the last visit.
- Collection of diary card
- Collection of blood for serology (and B cell studies on a subset of participants): 7.5 ml of whole blood. If less than 4mL of blood is collected, the whole sample will be used serology assays. If 4-6mL of blood is collected the sample will be split in half and shared evenly between serology assays and B cell studies (if applicable). If >6mL of blood is collected, 3mL will be used to provide at least 1mL of serum for serology assays, and the remainder will be used for B cell studies (if applicable).

**vii) Visit 7: Study month 11: Blood sampling visit at approximately 13 to 14 months, 28-42 days after booster vaccination**

- Reporting of SAEs that might have occurred since the Visit 5.
- Recording of any concomitant immunosuppressive medication or vaccines not foreseen by the study protocol
- Collection of blood for serology (and B cell studies on a subset of participants): 7.5 ml of whole blood. If less than 4mL of blood is collected, the whole sample will be used serology assays. If 4-6mL of blood is collected the sample will be split in half and shared evenly between serology assays and B cell studies. If >6mL of blood is collected, 3mL will be used to provide at least 1mL of serum for serology assays, and the remainder will be used for B cell studies.
- Administration of MMR

The vaccinees will be observed closely for at least 15 minutes, with appropriate medical treatment readily available in case of a rare anaphylactic reaction following the administration of vaccines.

viii) **Visit 8:** **Study month 22: Blood sampling visit at approximately 23 to 24 months, 11-12 months after booster vaccination**

- Reporting of SAEs that might have occurred since the Visit 7.
- Recording of any concomitant immunosuppressive medication or vaccines not foreseen by the study protocol
- Collection of blood for serology (and B cell studies on a subset of participants): 7.5 ml of whole blood. If less than 4mL of blood is collected, the whole sample will be used serology assays. If 4-6mL of blood is collected the sample will be split in half and shared evenly between serology assays and B cell studies. If >6mL of blood is collected, 3mL will be used to provide at least 1mL of serum for serology assays, and the remainder will be used for B cell studies.
- Study conclusion

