## 8.2 Reporting Procedures for All Adverse Events

All AEs attributed to the administration of DTaP-IPV-Hib, MenC-CRM197, MenC-TT, PCV13 and Hib-MenC observed by the investigator or reported by the participant, will be recorded on the CRF. All solicited and unsolicited adverse events will be recorded for 4 days following immunisation on diary cards. Unsolicited medically significant adverse events occurring between visit 1 and 4 will be recorded on diary cards, as will those occurring between visit 5 and 7.

The following information will be recorded: description, date of onset and end date, severity, assessment of relatedness to study medication, other suspect drug or device and action taken. The relationship of AEs to the study medication will be assessed by a medically qualified investigator.

All SAEs will be recorded through the whole study. Follow-up information should be provided as necessary.

These AEs considered to be related to the study medication as judged by a medically qualified investigator or the sponsor will be followed until resolution or the event is considered stable. All related AEs that result in a participant’s withdrawal from the study or are present at the end of the study, should be followed up until a satisfactory resolution occurs.

It will be left to the investigator’s clinical judgment whether or not an AE is of sufficient severity to require the participant’s removal from the study (see section 6.6). A participant may also be voluntarily withdrawn from the study by a parent/guardian due to what he or she perceives as an intolerable AE. If either of these occurs, the participant must undergo an end of study assessment and be given appropriate care under medical supervision until symptoms cease or the condition becomes stable.

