## 9.2 The Number of Participants

This is a non-inferiority trial assessing whether there is any difference in the antibody level between infants who receive no priming doses of MenC and those who receive 1 priming dose or 2 priming doses of MenC-CRM197.

The total sample size for the study is 498 participants randomised on a 10:10:7:4 basis to the 4 study groups. This will result in 160 participants in the Two Dose MenC group, 160 in the Single Dose MenC-CRM197 group, 114 in the Single Dose MenC-TT group, and 64 in 0 dose MenC (Control) group. Based on a mean (SD) log SBA of 3.47 (0.9) at 1 month after booster for 2 dose MenC12, 160 participants per group are required for the comparison between the Single Dose MenC-CRM197 and the Two dose MenC groups to detect 10% non-inferiority with a 2.5% level of significance (1-sided), 90% power and allowing for a 12.5% drop-out rate. An additional 114 participants will be required for the Single Dose MenC-TT group to allow a comparison with the Single Dose MenC-CRM197 primed group, allowing for a 12.5% drop-out rate.

No sample size calculation for the alternate limb component of the trial is included as the data generated here will be pilot data.

| Non-inferiority margi | Estimated difference | Power | Sample size required per group | Total sample size required |
| --- | --- | --- | --- | --- |
| 5% | -0.18 | 90% | 526 | 1052 |
|  |  | 80% | 393 | 786 |
| 7.5% | -0.26 | 90% | 253 | 506 |
|  |  | 80% | 190 | 380 |
| **10%** | **-0.35** | **90%** | **140*** | **280** |
|  |  | 80% | 105 | 210 |

** Requires 160 participants per group when allowing for a ‘dropout’ rate of 12.5%*

A previous study has shown the mean (SD) logSBA=2.85 (0.48) at 1 month following a 12 month dose of MenC vaccine with no prior MenC immmunisation43. Making the reasonable assumption that the SBA titres are relatively stable in the one month period after the vaccination, these statistics were used to calculate a sample size for a comparison between the one dose group and 0 dose control group at 6 days after the 12 month vaccination.

To detect a difference of 0.285 (10% of 2.85) between groups of equal size of 56 with a significance level of 0.05 (2-sided), would provide a power of 88%. Allowing for 12.5% drop outs, the initial size of 0 dose control group should be 64 infants. This therefore enables the 6 day blood test to be performed on only a subset of participants (64) in each of the other groups.

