# APPENDIX B: SCHEDULE OF PROCEDURES

| **Visit** | Visit 1 | Visit 2 | Visit 3 | Visit 4 | Visit 5 | Visit 6* | Visit 7 | Visit 8 |
| --- | --- | --- | --- | --- | --- | --- | --- | --- |
| Informed consent | X |  |  |  |  |  |  |  |
| Check inclusion criteria | X |  |  |  |  |  |  |  |
| Check exclusion criteria | X |  |  |  |  |  |  |  |
| Check elimination criteria |  | X | X | X | X | X | X | X |
| Check contraindications |  | X | X |  | X |  | X |  |
| Medical history | X |  |  |  |  |  |  |  |
| Vaccination history | X |  |  |  |  |  |  |  |
| Pre-vaccination body temperature | X | X | X |  | X |  | X |  |
| Randomisation | X |  |  |  |  |  |  |  |
| Blood sampling: for antibody and B memory cell determination (5ml at 5 months, 7.5ml for older ages) |  |  |  | X | X | X | X | X |
| Vaccination** | X | X | X |  | X |  | X |  |
| Daily post-vaccination recording of solicited symptoms (Days 0–3) by subjects’ parents/guardians | X | X | X |  | X |  |  |  |
| Return of diary cards |  | x | x | x |  | x |  |  |
| Diary card transcription |  | x | x | x |  | x |  |  |
| Record any concomitant immunosuppressive medication/ vaccination | X | X | X | X | X | X | X | X |
| Reporting of Serious Adverse Events |  | X | X | X | X | X | X | X |
| Conclusion of study |  |  |  |  |  |  |  | x |

* This would be for all participants in the Control Group (ie 64), and a matching number of participants in the Two Dose MenC, Single Dose MenC-CRM197 and the Single Dose MenC-CRM197 groups, as determined by randomisation at enrolment. Timelines: Visit 1: age 6-12 weeks, Visit 2: age approximately 3 months, Visit 3: age approximately 4 months, Visit 4: age approximately 5 months, Visit 5: age approximately 12 months, Visit 6:6 days after visit 5, Visit 7: age approximately 13 months, Visit 8: age approximately 24 months

** Vaccination as per study flow chart in Appendix A.

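### The booster diary card is scheduled for return only at Visit 6, which 242 of 498 children do not have; this conflicts with section 8.2 and with the planned booster safety comparisons

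*Protocol*

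**What the plan says.** **Issue of the card.** Section 6.3.6 has all children receive Hib-MenC and PCV13 at Visit 5 and has a four-day diary explained to the parents. Appendix B marks daily symptom recording (days 0 to 3) at Visit 5 with no restriction to a subset.

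**Return of the card.** After the booster, the visit lists in section 6.3.6 name diary collection only at Visit 6. That visit is described as "Blood sampling visit, at 6 days following Hib-MenC booster vaccination (Performed on 256 participants", made up of "all participants in the control group and 64 participants each from the Two Dose MenC, Single Dose MenC-CRM197 and Single Dose MenC-TT Groups". Appendix B agrees. Its return row reads "Return of diary cards | | x | x | x | | x", which covers Visits 2, 3, 4 and 6, with Visits 7 and 8 blank. The transcription row has the same pattern.

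**Visit 7.** This visit is for all children, 28 to 42 days after the booster. Its only adverse-event item is "Reporting of SAEs that might have occurred since the Visit 5".

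**What the diary is meant to cover.** Section 8.2 asks for all solicited and unsolicited events for four days after each immunisation. It adds that medically significant events between Visits 1 and 4 "will be recorded on diary cards, as will those occurring between visit 5 and 7".

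**What will be analysed.** Section 9.1 C tabulates events against the number of infants in each dose group. It also plans local and systemic comparisons after the booster: five dose-group contrasts and the limb contrast. None is limited to children who had Visit 6.

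**The concern.** In the infant phase each card is handed in at the next visit, which every child attends. The booster card breaks that pattern, because its only hand-in point is a visit held for a subset. The omission appears in the visit text and in two separate rows of Appendix B, so it does not look like one misplaced cross.

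Two things follow if sites work to the schedule:

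- Children without Visit 6 have no point at which their booster reactions enter the data, although section 9.1 C compares those reactions across whole groups. An analysis plan cannot recover data that were not collected, and section 9.5 states that missing data will not be accounted for.
- Children with Visit 6 hand the card in on day 6. That is late enough for the four solicited days, but it is three weeks or more before Visit 7, up to which section 8.2 wants medically significant events written on a diary.

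At stake are the booster part of secondary objective 8, the reaction comparison in the alternating-limb component, and the diary record of medically significant events between Visits 5 and 7.

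**Working it through.** **Inputs**

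- Section 9.2: "The total sample size for the study is 498 participants randomised on a 10:10:7:4 basis to the 4 study groups". The group sizes given there are 160 for Two Dose, 160 for Single Dose MenC-CRM197, 114 for Single Dose MenC-TT and 64 for Control.
- Section 6.3.6, Visit 6: 64 children per group, chosen by randomisation at enrolment.
- The footnotes to Appendices A and B name the MenC-CRM197 single-dose group twice and omit MenC-TT. Sections 6.1, 6.3.6 and 6.4.4 make clear that MenC-TT is meant, so the counts stand.

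**Reproducing the plan's figures**

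- 160 + 160 + 114 + 64 = 498.
- 4 × 64 = 256 at Visit 6.
- Basis for 64 per group: 56 / (1 − 0.125) = 64.

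All agree with the protocol.

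**Children with no scheduled return of the booster card** (group size − 64)

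| Group | Without Visit 6 | Share |
|---|---|---|
| Two Dose | 160 − 64 = 96 | 60.0% |
| Single Dose MenC-CRM197 | 160 − 64 = 96 | 60.0% |
| Single Dose MenC-TT | 114 − 64 = 50 | 43.9% |
| Control | 64 − 64 = 0 | 0% |
| All | 498 − 256 = 242 | 48.6% |

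**Loss of precision if only Visit 6 cards were available**

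At a common event rate, the variance of a risk difference is proportional to 1/n₁ + 1/n₂. The standard-error ratio is therefore

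ratio = √[(1/64 + 1/64) / (1/n₁ + 1/n₂)], with 1/64 + 1/64 = 0.03125.

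| Contrast | Full sizes | Calculation | SE ratio | Share of children kept |
|---|---|---|---|---|
| MenC-CRM197 vs Two Dose | 160, 160 | √(0.03125/0.01250) | 1.58 | 128/320 = 40% |
| MenC-CRM197 vs MenC-TT | 160, 114 | √(0.03125/0.01502) | 1.44 | 128/274 = 47% |
| Consistent vs alternating limb | 498 in all | √(498/256) | 1.39 | 256/498 = 51% |
| MenC-CRM197 or Two Dose vs Control | 160, 64 | √(0.03125/0.02188) | 1.20 | 128/224 = 57% |
| MenC-TT vs Control | 114, 64 | √(0.03125/0.02440) | 1.13 | 128/178 = 72% |

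The limb row assumes that the 1:1 split also holds within the Visit 6 subset. Drop-out at the same rate everywhere cancels from every ratio.

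**In percentage points**

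The protocol gives no reaction rates, so 30% and 50% are assumed. The 95% half-width is 1.96 × √[p(1 − p)(1/n₁ + 1/n₂)], ignoring attrition.

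| Contrast | p = 50%: all cards → Visit 6 only | p = 30%: all cards → Visit 6 only |
|---|---|---|
| MenC-CRM197 vs Two Dose | 11.0 → 17.3 | 10.0 → 15.9 |
| Limb (249 vs 249 → 128 vs 128) | 8.8 → 12.2 | 8.0 → 11.2 |

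**Time coverage for Visit 6 children**

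The solicited period is days 0 to 3 and the card is taken on day 6, so that period is complete. Section 8.2 recording runs to Visit 7, which falls on days 28 to 42. From day 6 to Visit 7 the schedule provides neither a card nor a later point at which to collect one.

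**The case against.** The best reply is that the intention is plain. Section 8.2 calls for a four-day diary after every immunisation and for diary recording up to Visit 7. Section 9.1 C counts all infants in each group. Every child is due at Visit 7, where a nurse could simply ask for the card. On that view this is a gap in a checklist, with no data lost. Medically significant events also have other routes: section 8.2 puts attributed events seen by the investigator or reported on the case report form, and serious events are asked about at Visit 7.

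Much of this stands, and it rules out several stronger conclusions that a reader might draw:

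- *Booster reactions are missing for 60%, 60%, 44% and 0% of the groups.* The protocol does not say so. Those are the shares with no scheduled return.
- *Return that differs by arm biases the comparisons.* The Visit 6 subset is drawn at random at enrolment, so within each arm the children with a scheduled return are a random sample. Restricting to them costs precision and does not by itself bias the contrasts.
- *Objective 8 as a whole would rest on half the children.* Cards for the 2, 3 and 4 month vaccinations are collected from all children at Visits 2, 3 and 4. Only the booster part is exposed.
- *Events after day 6 cannot be captured in the Visit 6 children.* Section 8.2 does not say that there is only one card, or that nothing stays with the family.

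The conflict itself remains. Section 6.3.6 and Appendix B agree with each other and disagree with section 8.2. Informal retrieval is also a poor substitute: if return depended on the site or the parent, the cards obtained beyond the Visit 6 subset would no longer be a random sample.

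**Conclusion.** The point holds as a contradiction in the procedures with a measurable cost. As written, 242 of 498 children (48.6%) have no scheduled return of the booster diary. The collection set for the remaining 256 does not fit the recording period in section 8.2. Followed to the letter, the schedule would leave the booster safety comparisons on 64 children per group. Standard errors would then be larger by a factor of 1.58 in the worst contrast (MenC-CRM197 vs Two Dose) and 1.13 in the mildest (MenC-TT vs Control).

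These factors assume that no card is obtained outside Visit 6, that event rates are similar in the groups compared, and that attrition is equal. If sites collect cards at Visit 7 anyway, the loss shrinks accordingly, possibly to nothing.

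Severity is moderate. The outcome is secondary, no power is claimed for it, and the limb component is described as pilot data. The primary endpoint, rSBA titres one month after the booster, is untouched.

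**What to change.** 1. In section 6.3.6, add diary-card collection to the Visit 7 list for all participants.
2. In Appendix B, mark Visit 7 in the return row and in the transcription row.
3. Reconcile the Visit 6 collection with section 8.2, so that the text says how recording continues to Visit 7 for children who have Visit 6. One option is to review the day 0 to 3 entries at Visit 6 and leave the card, or a continuation card, with the family.

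The cost is one line, two table cells and one clarifying sentence. Visit 7 already takes place for everyone, so no visit, blood sample or vaccination changes.
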